### Design

The experiment employs both between and within variation and is randomised through a block design (5 blocks). The first factor, which varies between participants, is the language condition. There are four main language conditions, and one sub-condition: singular masculine generics, singular feminine g- gender, gender inclusive binomial word-pairs, English gender neutral, and plural masculine generics as the sub-condition (see Table 1).

**Table 1 pone.0292936.t001:** Between variation and breakdown of conditions.

Condition		Example
**1.**	Singular generic masculine	مدرس ‘Teacher[+masc]’
**1.1**	Plural generic masculine	مدرسين ‘Teachers[+masc]’
**2**	Singular feminine	مدرسة ‘Teacher[+fem]’
**3**	Gender-inclusive: Feminine/Masculine word-pair	مدرسة/ مدرس ‘Teacher[+fem]/Teacher[+masc]’
**4**	Gender-neutral: English neutral	Teacher

There is one factor that varies within-participant and that is the ‘stereotypicality’ of the role. Role nouns can be associated with men (e.g., *manager*), associated with women (e.g., *nurse*), or neutral (e.g., *student*). All participants are presented with the same 12 role nouns (4 in each stereotype) but in different language conditions.

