The second component is considered an exploratory sub-experiment of the first which evaluates the effect of plural masculine generics on the occupational expectations of Egyptian Arabic speakers. The key difference between this component and the former is that this block does not test this relationship in other language conditions (such as feminine plurals or in binomial word-pairs) which would require 3 additional blocks instead of one. This component will be used to explore one key question: do plural masculine generics and singular masculine generics elicit the same male-bias in representation? Importantly, this exploratory sub-experiment has 6 experimental stimuli (in the masculine) compared to the other blocks (see Table 3). This is to ensure a balance of masculine and feminine priming throughout the experiment.

**Table 3 pone.0292936.t003:** Experimental block for the plural masculines.

Block	Male Stereotype	Female Stereotype	No Stereotype
**Block 4**	**مديرين** **Managers [+ masc]**	راقصة Dancer [+ fem]	تلميذة/تلميذ Student [+ fem/masc]
	محامية/محامي Lawyer [+ fem/masc]	**ممرضين** **Nurses [+ masc]**	مسؤولة مبيعات Salesperson [+ fem]
	دكتورة Doctor [+ fem]	**مضيفين طيران** **Flight Attendants [+ masc]**	**ممثلين** **Actors [+ masc]**
	**مهندسين** **Engineers [+ masc]**	عاملة نظافة Cleaner [+ fem]	**مغنيين** **Singers [+ masc]**

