## Materials

Experimental stimuli and role nouns have been selected based on a corpus collected from online Egyptian recruitment websites [11] and a large scale norming study on occupational stereotypes [35]. These roles were then cross-checked on Sketch Engine to ensure that none of the roles selected are low frequency. For an occupation to qualify as stereotypically female, it has to be typically advertised to women and advertised in feminine grammatical gender (such as *nurse* and *secretary*). Similarly, these roles on Sketch Engine were more likely to appear in feminine G-gender compared to their masculine counterpart, which further validates the stereotypicality of the role. For stereotypically male roles, the same approach was adopted, and occupations were selected if they mostly (at least 70%) targeted men and used masculine grammatical gender (such as *lawyer* and *manager*).

There were two main challenges when selecting the experimental stimuli. Firstly, the gendered stereotypes need to hold cross-culturally for both Egyptian and British participants. Secondly, as the existing corpus and literature has shown, Egyptian online recruitment is heavily gender segregated and polarised. Consequently, finding ‘neutral’ roles in the corpus proved to be difficult and therefore 3 of the neutral stimuli were selected based on other norming studies’ classifications [3, 35].

To mitigate these challenges and ensure that the stereotypes match the attitudes of the target sample(s), additional norming during the piloting stage will be conducted. This will consist of a simple questionnaire to be circulated amongst an Egyptian and British sample (n = 10 for each) asking participants to rate the occupations selected (this includes 4 plus an additional 2 ‘back-up’ role nouns in each stereotype) as stereotypically male, female, or neither on a 7-point scale. Role nouns with stereotypes that do not hold cross-culturally will be excluded from the experiment, with the target of having 4 occupations for each stereotype.

Non-experimental stimuli will include animals (such as *cat*) and will be G-gender balanced with 2 nouns presented in feminine G-gender and 2 presented in masculine G-gender.

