## Pre-specified analysis plan

The study uses mixed effects regression, modelled in STATA, to account for within and between variation in the experiment. There are two different outcome categories and therefore multiple models will be used to explore the effect of language on the dependent variables outlined above.

The first set of models related to fluency will utilise linear-mixed-effects models, and models related to gender expectations will use generalised linear mixed effects models for categorical dependent variables. In both cases, the language condition will be defined as the fixed effect. The models will include random slopes for this fixed effect as some occupations may be more affected by the language condition than others. By-participant random slopes and intercepts will be included in the models as random effects. This is because participant variation is expected due to differences in demographic information (age and gender), attitudes towards women (from the exit survey), language dominance measures (exit survey), and participant’s nationality (note that this is likely corelated with attitudes towards women, and highly correlated with language dominance measures). Similarly, by-item random slopes and intercepts will be included as variation due to length of stimuli or familiarity with different occupations should be accounted for.

Interaction effects will be explored between stereotype and language condition, and for a subsample of the data interactions between number and stereotype will also be explored. Interaction effects related to number will help assess the mediating effect of number on gender expectations in masculine grammatical gender.

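### The number analysis is assigned to an undefined subsample; if that means masculine prompts only, singular versus plural is wholly between persons and forgoes six shared prompts that could sharpen it, mainly for fluency

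*Protocol article*

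**What the plan says.** The Design section of the Protocol article gives every participant twelve role nouns: "All participants are presented with the same 12 role nouns (4 in each stereotype) but in different language conditions". Table 1 lists plural masculine as sub-condition 1.1, next to singular masculine, feminine and word-pair.

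Under Conditions, the second component (block 4, Table 3) is called exploratory. Its question is: "do plural masculine generics and singular masculine generics elicit the same male-bias in representation". Of its twelve prompts, the text states that "this exploratory sub-experiment has 6 experimental stimuli (in the masculine) compared to the other blocks" and explains: "This is to ensure a balance of masculine and feminine priming throughout the experiment". Table 3 prints only the six plurals in bold.

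The Pre-specified analysis plan makes language condition the fixed effect and adds: "By-participant random slopes and intercepts will be included in the models as random effects". By-item slopes and intercepts are planned as well. On number it says that "for a subsample of the data interactions between number and stereotype will also be explored", in order to assess "the mediating effect of number on gender expectations in masculine grammatical gender". The subsample is not defined.

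**The concern.** Number varies only among masculine prompts, and the stated target is number within masculine gender, so masculine prompts are the obvious candidate for the subsample. In that subset block 4 participants contribute plurals only, and blocks 1–3 contribute singulars only. A participant intercept then cannot separate how fluent a person is from the effect of number, and all between-person variation enters the contrast.

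The design already collects data that would help. The other six prompts in block 4 are given a role only as priming balance, but they are answered by the same 30 people and also appear in blocks 1–3. Singular versus plural is part of research question 1a, and the Hypotheses section predicts a more extreme effect in the singular. The plural side has a target of only 30 participants. Without the shared prompts, the number analysis is less precise than the data allow. It also has no internal check on whether block 4 participants answer differently in general.

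**Working it through.** **Inputs from the protocol.** Sample size section: at least 30 participants in each of blocks 1–4, plus 30 + 30 in the English block. The stated total is reproduced: 4 × 30 + 30 + 30 = 180. Tables 2 and 3 give the prompts. The protocol gives no effect size, SD or within-person correlation, and no precision figure for number.

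**Step 1: overlap.** Each non-plural prompt of Table 3 has an exact match in Table 2:

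| Block 4 prompt | Same noun and form in |
|---|---|
| Cleaner, feminine | Block 1 |
| Student, word-pair | Block 1 |
| Salesperson, feminine | Block 2 |
| Lawyer, word-pair | Block 3 |
| Doctor, feminine | Block 3 |
| Dancer, feminine | Block 3 |

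Blocks 1–3 each hold 4 masculine, 4 feminine and 4 word-pair prompts. Block 4 holds 6 plural masculine, 4 feminine and 2 word-pair prompts, and no singular masculine.

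**Step 2: trial counts.** Masculine only: 90 × 4 = 360 singular and 30 × 6 = 180 plural trials. Shared prompts in block 4: 30 × 6 = 180 trials. All Arabic trials: 120 × 12 = 1,440.

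**Step 3: masculine-only precision.** Assume a continuous outcome with total SD 1, a participant share of variance ρ and noun fixed effects. Each plural noun has its singular in exactly one of blocks 1–3, two nouns per block. Hence

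SE² = [ρ + (1−ρ)/6]/30 + [ρ + (1−ρ)/2]/90.

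- ρ = 0.2: 0.3333/30 + 0.6/90 = 0.01778, SE 0.133
- ρ = 0.4: 0.5/30 + 0.7/90 = 0.02444, SE 0.156
- ρ = 0.6: 0.6667/30 + 0.8/90 = 0.03111, SE 0.176

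**Step 4: all Arabic trials.** Generalised least squares on the exact layout of Tables 2 and 3, with form as a four-level factor (singular masculine, plural masculine, feminine, word-pair):

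| ρ | SE masculine only | SE all trials | Cut |
|---|---|---|---|
| 0.2 | 0.133 | 0.109 | 18% |
| 0.4 | 0.156 | 0.101 | 35% |
| 0.6 | 0.176 | 0.085 | 52% |

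With an added participant-by-form variance of 0.1 (residual 0.9 − ρ), the SE goes from 0.145 to 0.126, 0.167 to 0.120 and 0.186 to 0.108. These are cuts of about 14%, 28% and 42%.

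**Step 5: number by stereotype.** Allowing each form effect to differ by stereotype, the SE of the difference in number effect between two stereotypes goes from 0.237 to 0.210, 0.211 to 0.182 and 0.177 to 0.149 at ρ = 0.2, 0.4 and 0.6. These are cuts of 11%, 14% and 16%.

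**Step 6: nouns that differ in their number effect.** An assumed item-slope variance of 0.04 adds 0.04/6 = 0.0067 to both squared SEs. At ρ = 0.2 the SE then goes from √(0.01778 + 0.0067) = 0.156 to √(0.01195 + 0.0067) = 0.136, a cut of 13% instead of 18%. At ρ = 0.4 the cut is 26% instead of 35%.

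**The case against.** A reader might infer that the plan discards the six shared prompts. The text does not say so. The subsample could equally mean the Arabic blocks with the English block left out, in which case nothing is lost. The clause also concerns only the interaction of number with stereotype. The main model has language condition as its fixed effect, and Table 1 lists plural masculine among the conditions, so the singular–plural main contrast may already be fitted on all Arabic trials. The sentence on six stimuli can be read as a count of masculine prompts, six against four in the other blocks. In the Materials section only the fillers are named as outside the experiment: "Non-experimental stimuli will include animals". All of this stands. It makes the loss conditional on one reading, though the likeliest, and it leaves the 11–16% for the interaction as the figure most directly tied to the subsample clause.

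A reader might also infer bias. The Procedure section allocates participants at random among the blocks for which they are eligible, so a between-person comparison of 30 with 90 is unbiased, only less precise.

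Two further objections limit the benefit. The component's headline question is male bias, a gender-interpretation outcome, and four of the six shared prompts are feminine. The Hypotheses section predicts female readings for these whatever the role, so they say little about a person's tendency to read masculines as male. Second, block 4 has a different mix of forms and includes plurals, and the protocol itself allows that word-pairs may draw plural markers. Shared prompts may therefore not be answered alike in both contexts. This is a reason to check the assumption and to keep the masculine-only result beside the fuller one, not a reason to leave the data unused.

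**Conclusion.** The point holds as a cheap improvement in precision. The overlap of six prompts is exact, and on masculine prompts alone the number contrast is wholly between persons (30 versus 90). If the subsample is masculine prompts only, using all Arabic trials would lower the SE of the number main effect by about 18–52% at assumed intraclass correlations of 0.2–0.6, by about 14–42% with participant-by-form variance 0.1, and the number-by-stereotype SE by about 11–16%. By-item slopes, which the plan includes, would shrink the percentages for the main effect further.

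The figures rest on a continuous outcome, 30 participants per block without exclusions, assumed variance shares, and shared prompts that behave alike across blocks. They apply mainly to the fluency measures; little gain should be expected for gender interpretation. The documents do not support a claim that data are definitely thrown away or that the singular–plural comparison is biased.

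**What to change.** In the Pre-specified analysis plan, define the subsample. State that the number contrast and its interaction with stereotype are fitted on all Arabic trials of blocks 1–4, with form as a four-level factor (singular masculine, plural masculine, feminine, word-pair) and the participant and item random effects already planned, at least for the fluency outcomes. Report the difference between block 4 and blocks 1–3 on the six shared prompts as a check on context, and keep the masculine-only analysis as a sensitivity analysis.

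The cost is a sentence or two and no new data. The downside is the added assumption that block context does not alter responses to the shared prompts; the block comparison and the sensitivity analysis are there to expose a failure of it.

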### Outcomes of interest

To answer the research questions outlined above, the study focuses on two outcome categories: fluency measures and the participant’s gender interpretation of the prime.

Fluency measures consist of 5 dependent variables: the total number of words produced, hesitation markers, number of false starts, fluency mistakes, and initial response time. These measures are consistent with current literature on speech production [34]. The focus on fluency allows for exploration of processing costs and benefits due to in/congruent or asymmetric stimuli. Additionally, fluency measures help show what is easily accessed or recalled. Processing benefits are expected when participants’ S-gender expectations are not violated (i.e., a *secretary* in feminine morphology and a *manager* in masculine morphology compared to a *secretary* in the masculine). Importantly however, roles associated with women presented in masculine morphology should *not* result in processing costs if masculine G-gender is truly interpreted as generic or unmarked.

To measure the participant’s interpretation of the prime their responses will be coded based on the proportion of gendered morphosyntactic markers in their speech. Importantly, this will be weighted at the tensed phrase (TP) level. This is to avoid inflating scores based on morphosyntactic markers for the sake of agreement across noun phrases or verb phrases. This coding will be used to derive two other categorical variables to be used in the analysis: the participant’s gender expectations and whether the expectations are congruent with the social stereotype associated with the prime.

Example 3 provides a fictitious response to the stimulus “*manager [+masc]*” and how this would be coded. Firstly, we can see that there are three morphosyntactic markers that are masculine, two of which are used only for agreement purposes. Secondly, we can determine that the participant interpreted the stimulus to be a man and that this response is congruent with the prime (i.e., grammatical gender and social gender are not asymmetric).

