Thus far this research has been relatively limited to ‘Western’ contexts. This study aims to extend this research on grammatical gender and to test whether masculine generics in other language families, specifically Arabic, behave similarly to Indo-European languages. Arabic is one of the most spoken languages around the world, and yet research on the processing of Arabic grammatical gender remains relatively understudied. Additionally, the use of masculine generics in Arabic speaking countries, especially in the context of job recruitment and formal settings, is largely unquestioned and widely accepted as equally representative of all genders. However, a recent study on the language used in Egyptian job recruitment and advertising showed an overuse and inconsistent use of masculine generics, where stereotypically male-dominated industries used masculine generics and stereotypically female-dominated jobs were advertised in feminine grammatical gender regardless of the gender targeted for the role [11]. Additionally, the study showed that jobs were advertised in both singular (majority) and plural masculine generics, and so a key aspect of this investigation is to determine whether masculine generics in singular or plural are interpreted more or less strongly as male-referring. Therefore, the overall aim of this study is to explore how the presence or absence of grammatical gender affects gender representation in perception.

Specifically, the primary objective of this study is to investigate the role that morphological gender marking plays in either entrenching or perhaps mitigating these segregated and polarised recruitment patterns. To do so, we explore the following questions:

1. How does grammatical gender mediate referent expectations in the presence of competing social information?
a. Do singular masculine generics create a male bias in perception, and are these biases different in singular and plural masculine generics?b. Do participants rely more on stereotypical social information or grammatical information to inform their occupational expectations?c. If the social and grammatical cues conflict, do participants exhibit processing costs? Or is there a processing benefit to having congruent social and grammatical cues? And are these benefits or costs consistent across different gender and cue-type combinations?

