Similarly, in condition 4 (neutral English), stereotypical information may inform participants’ gender expectations, such that *doctors* are more likely to be men and *secretaries* are more likely to be women in responses. If this is the case, then the fixed effect for language in conditions 3 and 4 should not be statistically different. Importantly, in this condition participants have the option to respond in the gender neutral ‘they’ instead of assuming the role’s gender. Therefore, some variation between feminine, masculine, and neutral pronouns could be expected. If this condition also elicits highly gendered responses based on social stereotypes, then this presents evidence on the importance of gender-fair and representative language rather than just neutral language. This has implications for jobs advertised in English, which are assumed to be gender-neutral in interpretation but may instead entrench participant’s existing stereotypes.

Additionally, it is expected that fluency measures in congruent conditions will exhibit processing benefits (i.e., fewer fluency mistakes, more speech produced within the time limit, less hesitation, and reduced lag time) compared to their incongruent counterparts. Where grammatical information and stereotype information are incongruent (i.e., *nurse* presented in the masculine or *manager* presented in the feminine), it is predicted that outcomes related to fluency and initial response time will be negatively affected and participants will experience processing costs as a result of a violation of expectations. Importantly, interpreting masculine G-gender as generic should not be as costly or inefficient because it can be used to refer to male or female S-genders.

Further, condition 3 should not show significant differences in fluency or response time due to stereotype or number variation. This is because G-gender and stereotype information can always be congruent in a word-pair. Similarly in condition 4, it is predicted that fluency and response time will not vary across stereotype or number.

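### A processing cost for female-associated roles in the masculine is taken as evidence against a generic masculine, but the comparisons the plan implies would show the same difference from a congruence benefit alone.

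*Protocol article*

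**What the plan says.** All references are to the protocol article.

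- **Introduction, question 1c.** The plan asks whether conflicting cues carry a cost, and then: "Or is there a processing benefit to having congruent social and grammatical cues". It also asks whether costs or benefits are the same across gender and cue combinations. Cost and benefit are posed as alternatives.
- **Outcomes of interest, benefit.** "Processing benefits are expected when participants’ S-gender expectations are not violated". The example sets a secretary in the feminine and a manager "in masculine morphology compared to a *secretary* in the masculine".
- **Outcomes of interest, genericity.** The next sentence says that female-associated roles in the masculine should not "result in processing costs if masculine G-gender is truly interpreted as generic or unmarked". No reference for the cost is given.
- **Hypotheses, fluency.** "fluency measures in congruent conditions will exhibit processing benefits", and the comparison is "compared to their incongruent counterparts". A softer form of the genericity rule follows: "interpreting masculine G-gender as generic should not be as costly or inefficient because it can be used to refer to male or female S-genders".
- **Hypotheses, word-pairs.** "condition 3 should not show significant differences in fluency or response time due to stereotype or number variation". The reason given is that one member of the pair always matches the stereotype.
- **Table 5.** Each masculine and feminine fluency cell is coded only high or low. Within the masculine, female roles differ from male and neutral roles.
- **Pre-specified analysis plan.** A stereotype by language interaction is to be explored. No contrast or reference cell is tied to the genericity question.

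**The concern.** A congruence benefit and a cost of the masculine are different explanations with different meanings. If nurse[+fem] is easier than a neutral starting point and nurse[+masc] sits at that point, the masculine may be fully generic. If nurse[+fem] sits at the starting point and nurse[+masc] is harder, it is not. The plan defines the benefit against nurse[+masc] and looks for the cost in nurse[+masc], so on that comparison the two are one difference with the sign reversed.

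At stake are the fluency-based conclusion on whether masculine generics are generic, and the answer to question 1c. A result the plan itself predicts, a benefit for congruent prompts, would count against genericity even where the masculine costs nothing.

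**Working it through.** **Step 1. Two opposite explanations.** Take words produced, with an assumed baseline of 20 and an assumed effect of d words.

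- World A: masculine generic; congruent forms gain d. Nurse[+masc] = 20, nurse[+fem] = 20 + d, manager[+masc] = 20 + d.
- World B: masculine not generic; nurse[+masc] loses d. Nurse[+masc] = 20 − d, nurse[+fem] = 20, manager[+masc] = 20.

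| Contrast | World A | World B |
|---|---|---|
| nurse[+fem] − nurse[+masc] | d | d |
| manager[+masc] − nurse[+masc] | d | d |
| neutral[+masc] − nurse[+masc], neutral roles act as congruent | d | d |
| neutral[+masc] − nurse[+masc], neutral roles truly neutral | 0 | d |

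This holds for any d. The third row matters because Hypotheses says neutral roles in the masculine may behave as congruent. The within-masculine reading of Table 5 (rows 2 and 3) also compares different nouns, four per class.

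**Step 2. What the contrasts estimate.** Let C_m be the cost of the masculine on female roles and B_f the benefit of the feminine on them. Let n be any gain of neutral roles from the masculine, and p a cost of the word-pair common to all roles. Let g be any benefit of the pair specific to female roles, and q_N and q_F the penalties of a rarer feminine form on neutral and female roles. In words produced:

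- Feminine − masculine, female minus neutral nouns: C_m + B_f + n + (q_N − q_F).
- Pair − masculine, female nouns only: C_m + g − p.
- Pair − masculine, female minus neutral nouns: C_m + g + n.
- Feminine − pair, female nouns only: B_f − g + p − q_F.
- Feminine − pair, female minus neutral nouns: B_f − g + (q_N − q_F).

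The first contrast cannot separate C_m from B_f. The pair contrasts can, but only under assumptions about g, n, p and q.

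**Step 3. Size, as an illustration.** Inputs: Table 2 and 30 participants per block (Sample size). Over blocks 1–3, each stereotype class has 4 nouns × 30 = 120 observations in each of masculine, feminine and pair. With noun effects, form by stereotype and no participant variance, the interaction contrast has

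SE = √(4/120) = 0.183 residual SD.

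Adding a participant intercept with variance up to that of the residual raises this to 0.185. The pair contrasts net of neutral nouns have the same SE.

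Set C_m = 0, n = 0 and q_N = q_F, and assume B_f. By normal approximation with SE 0.185, the chance of a significant contrast in the direction of a masculine cost is Φ(B_f/SE − z):

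| B_f (residual SD) | B_f/SE | two-sided 0.05 (z = 1.960) | two-sided 0.10 (z = 1.645) |
|---|---|---|---|
| 0.3 | 1.62 | 37% | 49% |
| 0.5 | 2.70 | 77% | 85% |

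If the form effect also varies between nouns with an assumed SD of 0.2, the variance gains 0.2² × (1/4 + 1/4) = 0.020. Then SE = √(0.185² + 0.020) = 0.233, and the rates are 25% and 57% at 0.05, and 36% and 69% at 0.10.

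**The case against.** - **The comparator is inferred.** This is right: the genericity sentence names none. But Step 1 covers each comparison that the section and Table 5 suggest, and each is predicted to differ through a congruence benefit alone, the neutral one only if neutral roles act as congruent.
- **A reference level is a detail an article may leave out.** Fair for the reference level. The rule linking a cost to genericity, however, is in the article, beside a prediction that would produce the same pattern.
- **The softer rule asks only whether the masculine is less costly.** Comparing the two incongruence effects compares C_m + B_f with C_f + B_m, the corresponding sum for male roles. That speaks to costs only if B_f = B_m, which question 1c leaves open.
- **The size rests on assumptions.** It does. The benefits of 0.3 and 0.5 and the noun SD of 0.2 are not in the plan. The calculation omits the by-participant slopes that the analysis plan specifies. The plan gives alpha 0.1 for its later power analysis, not as a test level.

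Two stronger readings are tempting. A reader might infer that a feminine benefit will be taken as proof that the masculine is not generic. The documents do not go that far: the fluency rule is a conditional prediction, and the statement about confirming non-genericity stands mainly in the context of interpretation, which gendered markers measure separately. A reader might also infer that the design cannot separate cost from benefit at all. But Table 2 gives every noun a word-pair form and the stated interaction includes it, so a further contrast is available, though it depends on assumptions.

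**Conclusion.** The point holds for the fluency-based inference. As the rule and predictions stand, an apparent cost of the masculine on female-associated roles is expected whether the masculine is costly or the congruent form is merely easier. Question 1c is not answered by these contrasts. The male-bias evidence from marker proportions is untouched.

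The non-identification does not depend on sample size, alpha or effect size. The 37% and 77% only illustrate how often the pattern would reach significance under the assumed benefits.

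The word-pair is a usable but not a clean reference. The protocol's reason for expecting it to be stable across stereotypes, that it can always match, means it may itself carry the benefit (g above zero), which would return as an apparent masculine cost. Its predicted overall cost cancels only if it is common to all roles and neutral nouns are subtracted; subtracting them brings in n.

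**What to change.** 1. Call the masculine–feminine by stereotype contrast a congruence effect, and do not infer from it that the masculine is not generic.
2. As a secondary analysis that depends on assumptions, report masculine v word-pair and word-pair v feminine on the same nouns, each with and without subtracting the neutral nouns.
3. State the assumptions beside those results: the pair carries no stereotype-specific benefit; neutral nouns gain nothing from the masculine (Hypotheses says they may); and the lower frequency of feminine forms for male and neutral roles, which Hypotheses also notes, does not drive the feminine contrast.
4. If these assumptions are not accepted, claim only a congruence effect, and answer question 1c in those terms.

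The cost is wording, settled before the data are analysed. Participants, stimuli and model cells stay the same, and the pair contrasts net of neutral nouns are as precise as the masculine–feminine one (SE 0.183 to 0.185 residual SD). The downside is a narrower fluency-based conclusion about genericity.
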